**Figure 1 F1:**
[figure not shown]
Study design of the cross-over sham-controlled feasibility trial. Description of intervention arms: (1) TENSac (visit 2 active → visit 3 sham); (2) TENSsa (visit 2 sham → visit 3 active). (3) VNSac (visit 2 active → visit 3 sham). (4) VNSsa (visit 2 sham → visit 3 active). W-2, W0 and W2 are presented as an example of ‘plausible scheduling’. An interval of 1–2 weeks will be planned between visit 2 and visit 3, whereas no specific interval (*at least 1 week*) is required between visit 1 and visit 2. TENS, transcutaneous electrical nerve stimulation; tVNS, transcutaneous vagus nerve stimulation.

### Participants

The study includes eight adult men or women between 40 and 85 years old diagnosed with severe COPD (defined as forced expiratory volume in one second (FEV1)<50% of the predicted value (without including FEV1<20%), FEV1/forced vital capacity (FVC)<0.7 and smoking history of ≥10 pack-years, 3rd–4th grade dyspnoea (modified Medical Research Council (mMRC))^41^ for ≥6 months, COPD Assessment Test (CAT) score≥10),^42^ referred for pulmonary rehabilitation. Participants must exhibit the physical, psychological and mental capabilities to undergo submaximal constant work rate (CWR) exercise testing and answer the appropriate questionnaires. They must possess the ability to comprehend the implications of the procedures and follow-up visits and provide free informed consent.

Exclusion criteria encompass the presence of concurrent pulmonary restrictive features and neurological disorders susceptible to be influenced by neurostimulation procedures, including epilepsy, Parkinson’s disease, trigeminal neuralgia, dysautonomia and vagal disorders. Additionally, individuals with unstable arrhythmias, other cardiac instabilities or those with cardiac pacemakers, defibrillators or other metal implants, as well as those who have undergone pulmonary resection resulting in the absence of pulmonary lobe(s) or complete lung, are excluded. Furthermore, patients with COPD and other serious dyspnoeic conditions, such as lung cancer, anaemia, heart failure with reduced ejection fraction or mitochondrial dysfunction, will not be recruited for the present study. Pregnancy, active acute infections and known reactions or intolerance to tVNS or trigeminal TENS at the time of recruitment and visits also disqualify potential participants. Patients must have no moderate-to-severe exacerbations (defined as an increase in symptoms for more than 3 days requiring additional treatment (corticosteroids or antibiotics) compared with the usual regimen or hospitalisation)^43^ for at least 1 month before baseline visit and the first experimental visit (W0 visit). Participants who are randomised but experience an exacerbation between the first and second (W2) experimental visits will not complete the W2 visit. However, if the patient remains eligible and still consents, they may be re-randomised into the trial 1 month after the exacerbation, under the same pre-W0 visit conditions, and begin again from the W0 visit (table 1).

**Table 1 T1:** Participant inclusion and exclusion criteria

Inclusion criteria	Exclusion criteria
40–85 years	Neurological conditions: Epilepsy Parkinson’s disease Trigeminal neuralgia Dysautonomia Vagal disorders
FEV1 between 20% and 50% of the predicted value	Other medical conditions: Restrictive pulmonary syndrome Unstable arrhythmias Anaemia Heart failure with reduced ejection fraction Mitochondrial dysfunction Lung cancer
FEV1/FVC ratio<0.7	Pacemaker, defibrillators or other metallic implants
Smoking history of ≥10 pack-years	Lung resection surgery resulting in the absence of a lobe or a complete lung
Grade 3–4 on mMRC for ≥6 months	Pregnant women
CAT≥10	Active acute infection
Referred for pulmonary rehabilitation	Past reactions or intolerances to VNS or TENS
Physically, mentally and psychologically capable of undergoing CWR and answering questionnaires	Moderate-to-severe exacerbations in the last 1 month before the study visits

CAT, COPD Assessment Test; COPD, chronic obstructive pulmonary disease; CWR, constant work rate; FEV1, forced expiratory volume in one second; FVC, forced vital capacity; mMRC, modified Medical Research Council Scale; TENS, transcutaneous electrical nerve stimulation; VNS, vagus nerve stimulation.

### Study interventions

In the first arm (TENS), participants undergo submaximal CWR with the addition of a non-invasive trigeminal TENS, administered or expertly guided by a physiotherapy expert using the methods of this device. The TENS technique uses electromagnetic waves to modulate nerve transmission transcutaneously. When electrodes are placed on the skin, approximately over the temporomandibular joint, it is well established that they can modulate trigeminal nerve activity with the appropriate settings. We propose an initial configuration with a pulse duration of 60 µs at a frequency of 100 Hz, but the parameters may be adjusted during preliminary tests of the devices and for each patient as needed. For the sham trigeminal TENS, we suggest informing patients that two different modes of stimulation will be used, one of which will feel stronger than the other. This allows us to activate the device during the intervention and adjust it to a level where the skin experiences a mild tingling sensation. This stimulation will remain below the threshold of the gate control theory, being clinically ineffective, without explicitly informing the patients of this detail, in accordance with the attested consent form.^44^,^47^

In the second arm (tVNS), participants undergo submaximal CWR with the addition of cervical tVNS (*gammaCore Sapphire D Device, electroCORE*: Food and Drug Administration cleared^48 49^ and approved by *Health Canada*^50^). This technique will be applied or expertly guided by a neurosurgeon specialised in functional neurosurgery. The cervical tVNS device is applied manually to the front of the neck, near the trachea, to modulate afferent and efferent vagal nerve activity. As the *gammaCore* device is indicated and configured for the treatment of migraines, some parameters, such as a 5000 Hz pulse at 25 Hz, are fixed, while the stimulation voltage (limited to a peak of 24 V), and current (mA) remain adjustable and variable. This low-voltage VNS may be more advantageous for respiratory modulation.^51^

The effectiveness threshold, related to pain modulation, in terms of amplitude of the electrostimulation, depends on the patient. Then, for both tVNS and trigeminal TENS, the amplitude will be adjusted to reach a threshold where the patient perceives a strong stimulation, experiencing paraesthesia on the trigeminal area, while remaining comfortable for them.^52^ As an exploratory study, the initial stimulation parameters follow standard settings used for the device in their currently indicated conditions, but frequency, mode of stimulation (eg, burst, continuous), intensity and electrode placement remain open to investigation to expand knowledge in the field of dyspnoea neuromodulation. For the sham tVNS, the device will follow a similar procedure as the sham TENS. For both the sham and intervention, light and sound confounding stimuli on the devices will be used to enhance blinding efficiency and minimise the placebo effect in our comparative analysis.^53^ For the elaboration and application of the conceptualised sham-TENS and sham-tVNS by our research team, we thoroughly follow the *Template for Intervention Description and Replication (TIDieR)-Placebo reporting guideline*.^54^

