Transcutaneous electric nerve stimulation (TENS) is used in physiotherapy to treat various types of pain, such as trigeminal neuralgia, among its other uses.^28^,^31^ These treatments might be linked to the gate control theory studied in chronic pain, explaining that stimulation of particular neurologic structures may inhibit the intensity of other unpleasant afferences.^17 32 33^ Stimulation of the trigeminal nerve is supported by clinical practices such as the use of fans blowing cool air on patients’ faces, hypothesising that it activates nasal cold receptors in the V2 and V3 branches of the trigeminal nerve (cranial nerve V).^1733^,^35^ This suggests it could also be applied for other purposes, such as neuromodulation of dyspnoea.^36^

There is a recognised lack of alternative treatments for severe dyspnoea, and while opioids and other dyspnoea-directed therapies are often insufficient for alleviating this sensation, as they can be for pain management, neuromodulation may present a promising alternative.^37 38^ We hypothesise that neuromodulation techniques for relieving dyspnoea will be practical and well received by participants, and we aim to detect promising hints indicating that these methods can effectively reduce the sensation of dyspnoea. The main objective of this sham-controlled randomised trial is to evaluate the feasibility of this protocol, setting the stage for larger-scale research on the effectiveness of neuromodulation techniques for dyspnoea. The comparator in this randomised trial is a sham intervention using TENS and tVNS devices set to ineffective parameters, keeping participants blinded for a plausible study design.^39^

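### The active tVNS amplitude is titrated to paraesthesia in the trigeminal area, although tVNS is applied at the neck to reach the vagus nerve

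*Protocol article*

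**What the plan says.** All references are to the protocol article.

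**Active level.** Study interventions sets a single rule: "for both tVNS and trigeminal TENS, the amplitude will be adjusted to reach a threshold where the patient perceives a strong stimulation, experiencing paraesthesia", and the sensation is located by the words that follow, "experiencing paraesthesia on the trigeminal area, while remaining comfortable for them". The sentence before it ties the effective amplitude to pain modulation and says that it differs between patients.

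**Site of tVNS.** The same section states: "The cervical tVNS device is applied manually to the front of the neck, near the trachea, to modulate afferent and efferent vagal nerve activity". The pulse and the 25 Hz frequency are fixed by the device. Voltage, up to a 24 V peak, "and current (mA) remain adjustable and variable". The section then adds: "This low-voltage VNS may be more advantageous for respiratory modulation".

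**Sham level.** The Introduction says: "The comparator in this randomised trial is a sham intervention using TENS and tVNS devices set to ineffective parameters". For sham TENS, Study interventions has the device switched on and raised to mild tingling, and gives the reason: "This stimulation will remain below the threshold of the gate control theory, being clinically ineffective". For the other device it says only: "For the sham tVNS, the device will follow a similar procedure as the sham TENS".

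**Mechanism.** The Introduction gives vagus nerve stimulation a rationale based on pulmonary sensory afferents and parasympathetic signalling. It brings in gate control when it discusses TENS.

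**The concern.** Titrating to a sensation works only if the sensation arises where the device acts. Paraesthesia over the trigeminal area is a sensible endpoint for electrodes near the temporomandibular joint. For a device held against the front of the neck it is the wrong area. An operator who follows the text keeps raising output until the face tingles, the patient is uncomfortable or the device reaches its limit. An operator who sees the mismatch uses some other rule, which the document does not state.

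Either way, the document does not define the active tVNS dose in a form that fits the device. Acceptability and adverse effects, both under Secondary feasibility assessment, depend on that dose. So does the exploratory active-versus-sham comparison of Borg score and pedalling time. A larger trial that builds on this one would take over the same rule.

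The sham raises a lesser question of the same kind: whether a reason given for TENS supports the same label for tVNS.

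**Working it through.** No figure in the plan is in dispute, so the check sets the statements side by side and counts the tests affected.

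**1. Does the active endpoint fit each device?**

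| | Trigeminal TENS | Cervical tVNS |
|---|---|---|
| Site | Approximately over the temporomandibular joint | Front of the neck, near the trachea |
| Target nerve | Trigeminal | Vagus |
| Strong but comfortable sensation | Fits | Fits |
| Paraesthesia in the trigeminal area | Fits | Does not fit |

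The rule names both devices, so the last row cannot be read as applying to TENS alone.

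**2. What limits tVNS output if the rule is followed?** Pulse and frequency are fixed, so voltage and current are what the operator changes. The stated bounds are comfort and the 24 V peak.

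**3. How many tests are affected?** The abstract gives 4 patients per technique, each with one active and one sham test.

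- Experimental tests: 8 patients × 2 visits = 16, leaving aside any repeat visit for technical problems.
- Active tVNS tests: 4 × 1 = 4, and 4 / 16 = 25%.
- Sham tVNS tests: also 4 × 1 = 4 of 16.

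**4. Which outcomes are affected?** The primary outcome is the percentage of recruited patients who attend all visits and complete all tests. Its definition does not involve the titration endpoint. The secondary acceptability and adverse-event results for tVNS, and the exploratory tVNS contrast, do rest on the active dose.

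**5. What supports the ineffective label for sham tVNS?** The reason given is that stimulation stays below the gate-control threshold. It is stated for sham TENS and reaches tVNS only through the similar-procedure sentence. The amplitude threshold in the text is related to pain modulation. The Introduction's mechanism for vagus stimulation is a different one. So the document shows no reason, specific to tVNS and dyspnoea, why mild tingling should be without effect. That is absence of support for the label. It is not evidence that the sham works.

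**The case against.** The strongest defence of the active rule is practical. A functional neurosurgeon applies or guides tVNS and is unlikely to chase a facial sensation with a neck device. The core of the rule, strong but comfortable, suits the neck. Starting settings follow each device's current indication, and intensity and electrode placement are left open to investigation. All of this makes harm in practice less likely. It does not correct the text, which names the trigeminal area for both devices. Nor is this detail that an article leaves to the full protocol: it is a stated instruction that is wrong for one device.

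On the sham, the authors disclose in the strengths and limitations and in the Discussion that the procedure is not validated; the former adds that it was adapted from pain studies. They also say that they follow a placebo-reporting guideline, and they do state a patient-dependent amplitude threshold. This stands, and it reduces the sham point to wording. What the disclosure leaves out is that sham tVNS may be partly active.

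A reader might go further and see a contradiction between the ineffective sham and "This low-voltage VNS may be more advantageous for respiratory modulation". The documents do not support that. The sentence follows the description of a device capped at 24 V and refers to tVNS with that device as a whole. It does not say that every amplitude under the cap has a respiratory effect, and the source cited for it is not at hand. Nor do the documents give any value for sham activity, so no size of dilution can be derived.

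A reader might also want a zero-output sham. Patients could then feel the stimulation stop. They are the only blinded party (Trial design and study setting), Borg scores are subjective, and the Discussion already names unblinding as a risk of the cross-over. That would exchange a possible bias toward no difference for a likely loss of blinding.

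**Conclusion.** Wrong as written, on one point: the active tVNS endpoint names an area that does not match the device's site or target nerve. It affects 4 of 16 planned experimental tests, and through them the tVNS acceptability and adverse-event results and the exploratory tVNS contrast. The primary completion outcome is untouched, and the plan already disclaims efficacy (Sample size and feasibility; Discussion).

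The finding rests on reading the amplitude rule as it stands. If operators already titrate to sensation at the neck, the fault is in the text alone and no dose has been affected; the document does not say which is done.

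The sham point is secondary and concerns wording. The label is unsupported for tVNS, but nothing in the document shows that the sham is active or how active it might be.

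**What to change.** **Study interventions, active level.** Confine the trigeminal-area endpoint to TENS. For tVNS, set the active amplitude at the strongest comfortable sensation at the neck, within the 24 V peak. This is one clause and adds no visit, test or measurement. Because the trial is already recruiting, the clause should reach the operators as well as the text.

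**Introduction and Study interventions, sham tVNS.** Keep the sham procedure and describe it as *low-amplitude tVNS, presumed sub-therapeutic for dyspnoea*. Sham TENS needs no change.

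**Discussion, limitations.** Add that sham tVNS may be partly active, so a null tVNS contrast is not evidence against tVNS. The two sham changes cost wording only.

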### Outcomes

#### Primary (feasibility assessment)

Sample study completion proportion: percent of recruited patients attending all visits and completing all tests.

#### Secondary feasibility assessment

Acceptability of this study procedures (CWR, TENS, tVNS, etc) assessed by Likert score at the end of the last visit.Recruitment results: percent of recruited patients on the target sample size (which is 2 × n=4), and on the number of patients approached for screening.Numerical and descriptive occurrence of adverse effects and undesirable events throughout the complete study period, as reported by the patients and investigated by the researchers.

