#### Exploratory

Absolute change from baseline in maximum Borg score with a minimal clinically important difference (MCID)=1; and Borg score slope during test (measured every minute during CWR).Absolute change from baseline in pedalling time at the same pace and workload.Other statistical analysis of the data collected (questionnaires, test parameters, observations, etc) from participants to investigate the potential effect of neurostimulation (tVNS and TENS) on dyspnoea management.Assessment, through observational notes, of the ease of use and portability of VNS and TENS devices for patients with chronic pulmonary diseases.Assessment of the convenience and practicality of integrating VNS and TENS into their daily routines by patient-reported feedback (by Likert score and by free comments provided).Blinding assessment of the sham will be based on expectation and efficacy questions during visits and the conceptualised sham questionnaire at the end of the last visit.

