### Schedule of visits

Although this is a feasibility study focusing on recruitment, completion, adverse effects and acceptability (using a Likert questionnaire (online supplemental
appendix 1), our overarching research aims to explore the impact of dyspnoea in individuals by using the submaximal CWR^55 56^ at 80% of VO_2_ max to experimentally provoke dyspnoea symptoms and evaluate the effects of our proposed relieving techniques. According to the *American Thoracic Society 2019* standards,^57^ spirometry will be employed to evaluate pulmonary function, encompassing key parameters such as FEV1, FVC and FEV1/FVC. Basic vital signs, including oxygen saturation (SpO_2_), heart rate (HR), arterial blood pressure (BP), respiratory rate (RR) and temperature (T°), will also be measured to ensure the safety of the patients and to support the study. Subjective dyspnoea assessments will be carried out using the Borg scale (0–10) (online supplemental appendix 2),^58 59^ a 100 mm Visual Analogue Scale (VAS) for dyspnoea (online supplemental appendix 3) complemented by the mMRC dyspnoea scale for individuals with COPD (online supplemental appendix 4), the CAT questionnaire (online supplemental appendix 5), *St George’s Respiratory Questionnaire (SGRQ)* (online supplemental appendix 6) and the time to return to initial Borg Score serves as a measure of recovery following the exercise test. Data on rehabilitation performance will include measurements of workload, VO_2_ max, pedalling time and breathing and cardiac reserves. To confirm (yes or no) whether the baseline visit reached maximal effort at VO_2_ max, the criteria for maximal effort from the *European Respiratory Society (ERS) statement on the standardisation of cardiopulmonary exercise testing (CPET) in chronic lung diseases* will be applied*.*^60^ The quality of blinding with the proposed sham will also be assessed (online supplemental appendix 7). Other questions will assess participants’ expectations and perceived intervention efficacy during each exercise test using a Numeric Rating Scale (NRS) (online supplemental appendix 8). A short questionnaire will evaluate the anxiety, depression and catastrophisation related to breathlessness (online supplemental appendix 9). All the data expected to be collected are detailed in online supplemental
tables 1 and 2*.*

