Throughout the entire duration of the study, participants’ complete medication regimen will be assessed, and their medication must remain stable during the trial. As part of the pulmonary rehabilitation programme, the eight participants will undergo a medically advised first CPET at VO_2_ max following the data measurement procedures of the study. The Borg scale will be evaluated before the test, every 3 min during the test and at the end of the test. For the baseline visit, only SpO_2_ will be measured before and after CPET. Additionally, spirometry parameters, including FEV1, FVC and FEV1/FVC, will be measured before the test. Data on rehabilitation performance, such as VO_2_ max, breathing and cardiac reserve and the assessment of maximal effort testing, will be useful for the setting of the next two visits. This baseline CWR is crucial as it sets the parameters for the next two experimental visits and as it accounts for the effects of adaptation to the physical test (learning effect), ensuring that any observed changes in subsequent tests are not merely due to physiological adaptations or normal variations that occur in every test conducted under this protocol.

At least 1 week later, at the beginning of this first experimental visit, demographic data and medical records (confirmed via data entry form), the SGRQ and the Psychological Components Questionnaire will be administered. At this point, participants will receive either a cervical or facial neurostimulator, delivering cervical tVNS or trigeminal TENS. Then, they will undergo a submaximal CWR at 80% of VO_2_ max, with the intervention or the sham, and with the same data measurement of the baseline CWR with the addition of more dyspnoea evaluation questionnaires. These include the Borg scale assessed every minute during the test, the mMRC and CAT questionnaires administered before the test, and the VAS recorded before and after CWR. Participants’ expectations regarding the efficacy of the intervention will be assessed at rest, both with and without stimulation. At the end of the protocol, stimulation and perceived efficacy will be evaluated to gather additional subjective data on relief perception and the quality of the sham. Additionally, the time taken to return to the initial Borg score at rest following CWR will be measured. Vital signs, including SpO_2_, HR, BP, RR and T° will also be monitored throughout the entire duration of the test (except BP and T° that are only assessed before CWR).

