Within 2 weeks after the first experimental visit, those who received an intervention (tVNS or trigeminal TENS) will receive the sham, and those who received the sham will receive an intervention. This switch occurs according to the randomisation process of the cross-over group assignment (figure 1). They all undergo a final submaximal CWR, with data collected in the same sequence during the first experimental visit.

In case of technical issues or other concerns affecting the validity of the test or the data collected during one of the visits, an additional visit (W4) could be added after the last experimental visit. If this visit takes place, it will follow the same exercise testing and intervention protocols as the two preceding experimental visits.

If patients experience significant discomfort or adverse effects during the test or interventions, they should immediately inform the healthcare provider so that appropriate measures can be taken to reassure and manage the patient effectively, including possibly stopping the procedure if necessary. The exercise test termination criteria, established by the *American Thoracic Society*, will be followed to ensure participant safety.^56^ Otherwise, common short-term side effects will be assessed frequently, with a minimum of one evaluation at the end of each experimental visit using a standardised questionnaire designed for the interventions of the study. This approach aims to promptly identify and screen for any undesirable effects experienced by participants (online supplemental appendix 10).

Study visits will be completed before starting or before completing the 12-week rehabilitation programme, with a minimal interval to allow recovery after exercise testing while limiting external influences on exercise tolerance assessments. The schedule for data collection of each variable is detailed in online supplemental
table 3*.*

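### The acceptability Likert is timed only at the end of the last visit, so a patient who stops earlier gives no score and acceptability is estimated among completers only

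*Protocol article*

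**What the plan says.** All references are to the protocol article.

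- **Acceptability.** Under Secondary feasibility assessment, acceptability of the procedures (exercise test, TENS, tVNS) is "assessed by Likert score at the end of the last visit". No other time point is described.
- **Primary outcome.** Under Primary (feasibility assessment), it is the percentage of recruited patients who attend every visit and complete every test.
- **Side effects.** Under Schedule of visits, these are asked more often, "with a minimum of one evaluation at the end of each experimental visit using a standardised questionnaire".
- **Blinding.** Under Exploratory outcomes, this rests on "expectation and efficacy questions during visits and the conceptualised sham questionnaire at the end of the last visit". Schedule of visits adds that at the close of the first experimental visit "stimulation and perceived efficacy will be evaluated to gather additional subjective data on relief perception and the quality of the sham", and that the second experimental visit follows the same sequence.
- **A foreseen loss.** Under Participants, patients who "experience an exacerbation between the first and second (W2) experimental visits will not complete the W2 visit". If still eligible and willing, "they may be re-randomised into the trial 1 month after the exacerbation".

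**The concern.** Acceptability is the first-listed secondary feasibility outcome and is meant to guide a larger trial. The patient whose rating carries most information is the one who found the procedures hard to bear and did not come back. With the stated timing, that patient is the one without a rating. The measure depends on having stayed, which is what the primary outcome counts, so a favourable acceptability result could sit beside poor completion with no direct information on whether the two are linked.

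A lesser point concerns the sham questionnaire, which has the same timing. By then a completer has felt both the weaker and the stronger stimulation, so its answers describe blinding after cross-over, not how credible the first condition was to a patient who had nothing to compare it with.

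**Working it through.** **Inputs.** The target is 8 patients: 2 devices × 4 = 8, or 4 sequence groups × 2 = 8 under the 1:1:1:1 allocation. The figure reproduces. The article states no dropout rate, so the number of early leavers, d, is an assumption shown over a range.

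**Weight of one patient.** 1/8 = 12.5 percentage points.

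**Acceptability with d early leavers.** Suppose all 8 start stimulation and every completer finds the procedures acceptable.

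- Planned timing: (8 − d)/(8 − d) = 100% for any d below 8.
- Lowest possible value over all 8, if no early leaver accepts: (8 − d)/8.

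| d | Planned timing (exact 95% lower limit) | Lowest value over all 8 (exact 95% CI) |
|---|---|---|
| 1 | 7/7 = 100% (59%) | 7/8 = 87.5% (47% to 99.7%) |
| 2 | 6/6 = 100% (54%) | 6/8 = 75% (35% to 97%) |
| 3 | 5/5 = 100% (48%) | 5/8 = 62.5% (24% to 91%) |

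The value over all 8 lies between the last column and 100%, depending on what the early leavers would have answered. The planned timing cannot tell these apart.

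**How likely is at least one early leaver?** With an assumed loss rate q per patient, independent between patients, the chance is 1 − (1 − q)^8:

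- q = 5%: 34%
- q = 10%: 57%
- q = 20%: 83%
- q = 30%: 94%

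**What an early leaver does contribute.** A patient who stops after the first experimental visit has given the side-effect form and the expectation, perceived-efficacy and sham-quality ratings of that visit. These ratings attach to a known condition, active or sham. What is missing is the acceptability Likert and the sham questionnaire.

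**Does the restart rule close the gap?** No. It is optional and applies to exacerbations only. It does not cover a patient who withdraws because of discomfort or burden.

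**Meaning of the last visit.** The text does not say whether this is the last scheduled visit or the patient's own last visit. The second meaning helps only if withdrawal is known while the patient is still present. Someone who attends visit 2 and then does not return would not have been given the form.

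**The case against.** The strongest reply has four parts.

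1. **The losses are visible anyway.** In the example, completion of 6/8 would be reported beside acceptability of 6/6, and adverse events are recorded throughout. This stands in part: a careful reader would see that two patients are missing. It does not supply their opinion, and side effects are not acceptability.

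2. **The outcome concerns the whole protocol, so a rating after everything has been experienced is natural.** That stands as a reason to keep the final rating. It is no reason to have none from those who stop sooner.

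3. **Blinding is not left to the final questionnaire.** This stands. A reader might infer that blinding before cross-over goes unassessed, or that drop-outs are asked nothing. The article supports neither: expectation, perceived efficacy and quality of the sham are rated at each experimental visit, including the first.

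4. **The questionnaires may separate the conditions.** This also stands. A reader might infer that end-of-study answers cannot be assigned to active or sham. The items are in appendices 1 and 7 and the collection schedule is in supplemental table 3, none of which is at hand. A form completed after both visits can ask about each in turn. A single retrospective rating risks blending the two conditions, but the article does not show that this will happen.

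A tempting remedy is to ask patients at visit 2 whether they think they had active or sham. Under Study interventions, patients are told only that two modes of different strength are used, and are not told that the weaker one is ineffective. Such an item could reveal the sham just before visit 3.

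**Conclusion.** The concern holds for the acceptability Likert. As the article is written, this outcome comes only from patients who reach the last visit and is probably biased upwards. With 2 early leavers it could read 100% when the value over all who started is as low as 75%; with 1 or 3, the lowest value is 87.5% or 62.5%. These figures assume that all completers accept and that the early leavers do not, and the number of leavers is assumed. The direction of the bias rests on the judgement that those who stop are less likely to find the procedures acceptable. If every patient completes, there is no bias.

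For blinding, the point is one of labelling: data from before cross-over are planned, and the end-of-study questionnaire should not be read as if it were one of them. The matter is worth correcting because the remedy is cheap, but it does not affect the trial's structure or its primary outcome.

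**What to change.** - Give the acceptability Likert at the end of each experimental visit, together with the side-effect questionnaire already used there, and at early withdrawal. Say what is meant by the last visit.
- Report acceptability with all patients who started stimulation as the denominator, and state how many did not reach the last visit.
- Report the expectation, perceived-efficacy and sham-quality ratings from the first experimental visit as the before-cross-over blinding result. Label the end-of-study sham questionnaire as after cross-over.
- Do not add an active-or-sham guess item at visit 2 unless it is first reconciled with what patients are told about the two modes.

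The cost is one short form repeated once per patient, plus a contact at withdrawal for anyone who leaves. The blinding change needs no new data.
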